#### Interim analyses

This study does not consider interim analysis. If side effects occur frequently, the intervention will be stopped, and the report will be submitted to the Ethics Committee of Mashhad University of Medical Sciences (MUMS) for decision-making.

#### Methods for additional analyses (e.g., subgroup analyses)

In this study, subgroup analysis will be performed on participants with overweight (BMI between 25 and 30 kg/m^2^) and obese (BMI > 30 kg/m^2^) subgroups. Subgroup analysis will be performed using binary logistic regression adjusting for BMI.

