### Outcomes

The primary outcome of this trial will be the comparison of the acute effects of the two test meals on appetite response, and energy metabolism parameters, including resting energy expenditure (REE), DIT, and SO, and arterial stiffness indices (PWV and PWA) in overweight and obese men.

The secondary outcome is to compare the effects of two test meals on postprandial lipemia, including free fatty acids (FFA), low-density lipoprotein (LDL), high-density lipoprotein (HDL), total cholesterol (TC), and triglycerides (TG), glycemia (blood glucose), and insulinemia (serum insulin) in overweight and obese men.

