## Data collection and management

### Plans for assessment and collection of outcomes

#### Indirect calorimetry

RMR (kcal/d), DIT (kcal/d), and SO (g/d) will be measured by IC. To do calorimetry, participants will be asked to lie down in the supine position while awake and immobile; then, air samples will be collected using a mask (MetaLyzer 3B-R3 device), and respiratory gas (O_2_ and CO_2_) exchange will be measured for 20 min in the fasting phase, followed by postprandial measurements 60, 180, and 300 min after consumption of the test meals. The IC will be calibrated before the start of the measures.

The respiratory quotient (RQ) is the ratio of VCO_2_ to VO_2_ (VCO_2_/VO_2_), which reflects the rate of SO. DIT is the production of heat related to SO during energy uptake. DIT varies according to the quantity and type of oxidized substrate (i.e., carbohydrates, proteins, and fat).

IC will be performed in a quiet area at room temperature and mild lighting and require specific conditions (i.e., free of physical activity and psychological stress, fasting state for more than 6 h before the measurement, and resting in the supine position for > 20 min before the calorimetry). During the measurement, the room temperature will be maintained between 23 and 25 °C.

Given that stress has a negative effect on the quality of the calorimetry, the following measures will be taken to minimize the stress level of the participants:Performing the test in a completely quiet roomProviding facilities for the participants to rest in the intervals between assessments and at least half an hour resting before the testIn case of determining stress and tension in participants, testing will be postponed to another day

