#### Pulse wave analysis and pulse wave velocity

An ultrasound evaluation of the carotid artery will be done in the supine position, with the head turned 45° away from the scanning side. PWA and blood pressure measurement will be conducted using the Sphygmocor XCEL device on the right side of each participant. Blood pressure will be measured after at least 15 min of rest on the right upper arm. Moreover, the measurement of augmentation index (AIx), central blood pressure (cBP), and heart rate (HR) will be done according to the manufacturer’s guidelines for pulse wave analysis. As AIx is inherently heart rate dependent, the AIx75, which standardizes AIx to a heart rate of 75 beats per minute, will also be used.

Furthermore, arterial stiffness measurement will be taken using the tonometer at the femoral and carotid arteries, which give carotid-femoral PWV.

PWV will be examined according the sequentially measured electrocardiogram-gated left carotid and radial waveforms (applanation tonometry) using the stepwise method. The travel distance of the pulse wave will be calculated as the distance from the suprasternal notch to the femoral artery and the distance from the suprasternal notch to the carotid artery using a flexible tape measure. The measurements will be performed at least twice, and the mean PWV will be applied to the analysis. PWV will be measured at baseline and 30, 90, 210, and 330 min after the test meals.

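### The BMI subgroup analysis is specified as binary logistic regression adjusted for BMI, but no outcome is binary and that adjustment does not test whether the meal effect differs by BMI

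*Protocol article*

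**What the plan says.** The section on methods for additional analyses announces that "subgroup analysis will be performed on participants with overweight (BMI between 25 and 30 kg/m^2^) and obese (BMI > 30 kg/m^2^) subgroups". It then names the method: "Subgroup analysis will be performed using binary logistic regression adjusting for BMI". It gives no dependent variable, no cut-point and no meal-by-BMI term.

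The Outcomes section lists the primary outcomes as "appetite response, and energy metabolism parameters, including resting energy expenditure (REE), DIT, and SO, and arterial stiffness indices (PWV and PWA"). The secondary outcomes are free fatty acids, three cholesterol measures, "triglycerides (TG), glycemia (blood glucose), and insulinemia (serum insulin) in overweight and obese men".

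The assessment sections give scale and timing. For calorimetry, "RMR (kcal/d), DIT (kcal/d), and SO (g/d) will be measured by IC", with a fasting reading "followed by postprandial measurements 60, 180, and 300 min after consumption of the test meals". For arterial stiffness, "PWV will be measured at baseline and 30, 90, 210, and 330 min after the test meals". Appetite is rated before the meal and hourly afterwards on five instruments, one of which is a category scale. Blood is drawn before the meal and at 60, 120, 180 and 300 min.

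Under Trial design, each man eats both meals. The statistical methods section plans a repeated-measures generalized linear mixed model in PROC GLIMMIX, with time and protein source as the factors.

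**The concern.** Logistic regression needs a two-valued response, and this trial has none. An analyst following the sentence must cut a quantitative outcome at a point the plan does not give, or make meal or BMI class the response, which answers a different question. In the first case the choice of cut-point is open after the data are seen.

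The second part of the sentence does not rescue it. The subgroup question is whether the animal–plant difference is the same in overweight and obese men. A main-effect adjustment for BMI yields one meal effect common to both groups. Only an interaction between protein source and BMI addresses the difference, and none is named.

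At stake is the subgroup statement itself. It would rest on an arbitrary dichotomy, and the comparison of the two groups would not be tested.

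**Working it through.** **1. Is any outcome binary?** Comparing the subgroup section with the outcome and assessment sections:

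| Outcome | Form in the article | Binary? |
|---|---|---|
| RMR/REE, DIT | kcal/d, fasting and 60, 180, 300 min | No |
| Substrate oxidation | g/d, same times | No |
| PWV | velocity, baseline and 30, 90, 210, 330 min | No |
| PWA indices | augmentation index, central pressure, heart rate | No |
| Appetite | five scales, one of them a category scale, hourly | Not stated to be |
| Lipids, glucose, insulin | serum levels, baseline and four later samples | No |

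No threshold or responder definition appears for any of them.

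**2. What does dichotomising cost?** The article gives no cut-point, so a median split is assumed for illustration. For a normal outcome it keeps 2/π = 0.64 of the information, a loss of 1 − 0.64 = 0.36.

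**3. Does adjusting for BMI reveal effect modification?** This was simulated with 46 men, an assumed 23/23 BMI split, SD 330, within-person correlation 0.5, mean meal effect 250 kcal/day and 1,000 runs per scenario. REE was cut at its median and fitted by logistic regression with meal and BMI group as main effects. This pooled model is one reading of the sentence.

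| True interaction (kcal/day) | Mean meal coefficient (log-odds) |
|---|---|
| 0 | 1.26 |
| 250 | 1.23 |
| 400 | 1.21 |

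The reported coefficient hardly moves whether or not the meal effect differs by BMI. With an interaction term added and clustering by man allowed for, the dichotomised model has about 39% power for an interaction of 250 kcal/day. Comparing the undichotomised within-person differences between BMI groups has about 72%.

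**4. What could a correct interaction test detect?** The plan's own sample size reproduces first:

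m = 2(1.96 + 0.84)² × 330² × [1 + 4(1 − 0.5)] / (4 × 250²) = 20.49, rounded up to 21. With 10% dropout, 20.49/0.9 = 22.8, rounded up to 23 per group, or 46 in all. This does not depend on the subgroup method.

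For the interaction, take one REE measure and a within-person difference SD of 330. If 330 is instead the SD of a single reading, correlation 0.5 gives 330 × √(2 × 0.5) = 330, the same value. The detectable interaction at 80% power, two-sided 5%, is

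(1.96 + 0.84) × 330 × √(1/n₁ + 1/n₂).

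The article gives no BMI distribution, so the splits below are assumptions. Completers are 46, or 46 × 0.9 ≈ 41.

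| Completers | Assumed split | Detectable interaction (kcal/day) | Power for 250 kcal/day |
|---|---|---|---|
| 46 | 23/23 | 273 | 73% |
| 46 | 14/32 | 296 | 66% |
| 46 | 9/37 | 344 | 53% |
| 41 | 20/21 | 289 | 68% |
| 41 | 12/29 | 317 | 60% |
| 41 | 8/33 | 364 | 49% |

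Every value exceeds the 250 kcal/day on which the trial is sized.

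**The case against.** The best defence is that the sentence concerns an additional analysis. It features in neither the objectives, the outcomes nor the sample size, so the main comparison does not depend on it. That stands, and it limits the severity.

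The subgroup wording can also be read as separate fits within each BMI group, giving one meal estimate per group. That is a fair reading, and the pooled simulation does not describe it. But separate fits still need an undefined cut-point, and two separate estimates are not a test of their difference.

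Several stronger readings are tempting, and the article does not support them:

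- **Every outcome is continuous.** One appetite instrument is a category scale. The accurate statement is that none is defined as binary.
- **Logistic regression could never address the question.** It could, with a defined binary outcome, an interaction term and allowance for within-man correlation. The point is that the stated method supplies no binary outcome and names only a BMI adjustment.
- **The analysis ignores pairing and gives wrong standard errors.** The subgroup section is silent on correlation, and PROC GLIMMIX can fit a binary model with subject effects. A reader might attach a standard-error ratio of 1/√(1 − 0.5) = 1.41, but that belongs to a continuous outcome. After a median split at correlation 0.5 the binary correlation is (2/π) × arcsin(0.5) = 1/3, and the ratio would be 1/√(1 − 1/3) ≈ 1.22. Neither figure is needed here.
- **The detectable interaction measures the harm done by logistic regression.** It describes the power of the corrected analysis and shows only why that analysis should be called exploratory.

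One branch of the carryover plan restricts the comparison to the first period. There each man contributes one meal, and the paired figures above do not apply.

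**Conclusion.** The concern holds. The article explicitly fixes a method for binary data in a trial without a binary outcome, and it adjusts for the variable that defines the subgroups instead of testing its interaction with protein source. Because the method is stated, this is not a matter of detail left to an unseen analysis plan.

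The size is moderate. The 36% information loss assumes a median split. The detectable range of 273 to 364 kcal/day assumes a single REE measure, a within-person difference SD of 330, both periods used, and the BMI splits tabulated. The sample size calculation itself uses four repeated measures, so the range is illustrative. A reader might infer that the trial's main result is compromised; it is not, because the planned mixed model and the sample size of 46 are unaffected. This is a should-fix in an additional analysis.

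**What to change.** Delete the logistic regression sentence and replace it with wording such as:

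*Effect modification by BMI will be examined by adding BMI subgroup (overweight, obese) and its interaction with protein source to the repeated-measures mixed model. The estimated difference between the animal- and plant-protein meals in each subgroup, with its 95% confidence interval, and the interaction test will be reported as exploratory. BMI as a continuous modifier may be examined as a sensitivity analysis.*

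The same edit should assign a BMI of exactly 30 to one group, since the present definitions, "overweight (BMI between 25 and 30 kg/m^2^) and obese (BMI > 30 kg/m^2^) subgroups", do not place it clearly. It should also say what becomes of the subgroup analysis if the comparison is confined to the first period.

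The cost is a few lines of text, with no extra data, visits or participants. The Trial status section says enrolment has not begun, so the change can be made before any data exist.

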#### Analytical method to handle protocol non-adherence and any statistical methods to handle missing data

Since this study is performed in the acute phase, if participants do not adhere to the protocol, they will either be excluded from the study or asked to repeat the study on another day. Therefore, all the analyses will be done based on the per-protocol principle.

#### Plans to give access to the full protocol, participant level-data and statistical code

We strive to publish the complete study protocol and results as soon as possible, regardless of the extent or direction of the effect. The corresponding author may provide an anonymized data set and statistical code (Email: [contact]) on reasonable request.

### Oversight and monitoring

#### Composition of the coordinating center and trial steering committee

The ethics committee and Vice Chancellor of Research and Technology of the Mashhad University of Medical Sciences will supervise and organize all stages of the study. This is an academic committee without conflicting interests.

#### Composition of the data monitoring committee, its role and reporting structure

The Ethics Committee of MUMS will be fully informed from the first version of the protocol to the end of the research process and will control the accuracy of the trials at least twice.

#### Adverse event reporting and harms

Severe adverse events are not anticipated in this study; however, potential minor events may happen, which will be reported to the Ethics Committee of Mashhad University of Medical Sciences (MUMS) for further decisions.

#### Frequency and plans for auditing trial conduct

The study protocol will be evaluated by a team of research ethics professionals, and the procedure of the study will be evaluated by the assigned supervisor when 5% of the study participants are recruited based on the university regulations. Finally, the study procedure will be assessed at the end of the study by the same evaluation team.

#### Plans for communicating important protocol amendments to relevant parties (e.g., trial participants, ethical committees)

Each modification to the protocol that may affect the running of the study will be approved by the ethical committee of MUMS before implementation.

#### Dissemination plans

The procedure of the submission and approval of the reports for dissemination via journal publication will last about 4–6 months, and the results will be disseminated regardless of the direction or magnitude of their effects. Moreover, all the conditions associated with publishing the trial results pertain to the corresponding author, and there are no publication restrictions imposed by the sponsor.

## Discussion

Obesity is a global health issue with a tremendous economic burden [33]. As obesity is mainly due to an imbalance in energy intake and expenditure, identifying ways to reduce energy intake may help in successful weight reduction and weight maintenance strategies. As appetite plays a vital role in energy intake, it is a potential target for dietary interventions to reduce weight. Protein was previously found to reduce appetite, and high-protein diets resulted in a greater weight reduction compared to low-calorie diets with different food compositions [9, 10]. Protein intake from different sources may affect differently on metabolism and appetite [17, 34]. There is inconsistency regarding the effects of various protein sources on appetite and REE. Therefore, identifying the sources of protein that have the maximum impact on REE and appetite may help design dietary interventions for overweight/obese individuals. This study was designed to fill the gap of knowledge in this regard.

The novelty of this study is related to the assessment of the pure effect of a high-protein meal of different sources on short-term REE and appetite. As this study will evaluate the effects in a controlled laboratory setting, the possible significant differences can be attributed to the protein sources.

The findings of this study will provide novel insight regarding the thermogenic effects of different protein sources and their impact on postprandial satiety. The results of this study will help dieticians develop effective and efficient meal plans to improve weight reduction and maintenance in overweight/obese individuals.

Investigating the impact of a high-protein meal with different protein sources on PWV will allow a better understanding of the acute effects of these nutrients on the CVD risk factors, and it may shed light on the effects of long-term dietary lifestyles on the risk of CVD. These data can then be used as a reference for further studies on short-, medium-, and long-term effects of different protein sources on CVD risk factors and the incidence of CVD. Furthermore, the findings of this study may be used to identify the possible confounders (protein source) that might have an acute effect on PWV and to update the standard procedures before performing arterial stiffness measurements.

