#### Intervention description

Intervention condition A: participants will receive an AP test meal. The test meal will provide 20% of the calculated total daily energy requirements and will consist of 30% protein (from animal sources), 40% carbohydrate, and 30% fat.

Intervention condition B: participants will receive a PP test meal. The test meal will provide 20% of the calculated total daily energy requirements and will consist of 30% protein (from plant sources), 40% carbohydrate, and 30% fat.

To estimate the total daily energy requirements of the subjects, the Harris–Benedict Eq. [31] will be used as follows:For women—BMR = 655.1 + (9.563 × weight in kg) + (1.850 × height in cm) − (4.676 × age).For men—BMR = 66.5 + (13.75 × weight in kg) + (5.003 × height in cm) − (6.75 × age).

After calculating BMR by the above formula, TEF and physical activity will be added to calculate TEE.

The test meals will be prepared in the Nutrition Department kitchen at the Mashhad University of Medical Sciences, Mashhad, Iran. The composition of the test meals is presented in Table 2. Two test meals will be isocaloric and similar in macronutrient and fiber content. The palatability of the test meals will be measured using the visual analog scale (VAS). The viscosity of the meals will be measured using a Brookfield Synchro-Lectric Viscometer (Brookfield Engineering Laboratories, Inc.).

**Table 2 Tab2:** Ingredient composition of the test meals

	**AP**	**PP**
**Protein source**	Chicken breast, egg, yogurt	Soy protein
**Other ingredients**	White toast, potato, carrot, pickled cucumber, parsley, sunflower oil	White toast, mushroom, bell pepper, onion, tomato paste, sunflower oil

*AP* animal-based protein, *PP* plant-based protein

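### The two test meals differ in most of their non-protein ingredients as well as in protein, so the trial can compare two whole meals but cannot attribute a difference to protein source alone

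*Protocol article*

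**What the plan says.** The Discussion gives the trial's novelty as the "assessment of the pure effect of a high-protein meal of different sources on short-term REE and appetite". The next sentence gives the ground for causal attribution: because the effects are studied under laboratory control, "the possible significant differences can be attributed to the protein sources". Both stated objectives, primary and secondary, are worded as effects of dietary protein source, and the section on statistical methods names protein source as a model factor.

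The recipes are in Table 2, under Intervention description. The animal-protein (AP) meal takes its protein from "Chicken breast, egg, yogurt" and the plant-protein (PP) meal from soy. The other ingredients are:

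- AP: "White toast, potato, carrot, pickled cucumber, parsley, sunflower oil"
- PP: "White toast, mushroom, bell pepper, onion, tomato paste, sunflower oil"

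On matching, the same section says: "Two test meals will be isocaloric and similar in macronutrient and fiber content". Each meal has the same planned energy split of 30% protein, 40% carbohydrate and 30% fat. Palatability and viscosity are measured, and the two meals are compared on them by *t* test. The section on choice of comparators states that there is no control condition.

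**The concern.** Laboratory control and a crossover remove differences in setting and between persons. They do nothing about differences between the meals themselves. If the meals differ in more than their protein, a difference in energy expenditure or appetite may come from the protein, from what accompanies it, or from both together.

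What is at stake is the trial's main conclusion. The article expects its findings to guide dieticians in planning meals according to protein source. A reader who accepts the attribution sentence would credit the protein with an effect that this design cannot assign to it, however well the trial is run.

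**Working it through.** The plan gives no figure to reproduce. The check is a count from Table 2, followed by a question of what is estimable.

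**Step 1. Count the ingredients.**

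| Non-protein ingredients | Which | Number |
|---|---|---|
| In both meals | sunflower oil, white toast | 2 |
| In AP only | parsley, carrot, potato, pickled cucumber | 4 |
| In PP only | onion, mushroom, tomato paste, bell pepper | 4 |

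- Listed per meal: 2 + 4 = 6.
- Distinct over both meals: 2 + 4 + 4 = 10.
- In one meal only: 4 + 4 = 8, that is 8/10 = 80%.
- Within each meal, absent from the other: 4/6 = 67%.

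**Step 2. What is matched.** Total energy is the same by design, and macronutrients and fibre are stated to be similar. Gross composition is therefore not a ready explanation of a difference. The article states no matching of the kind of carbohydrate food or of the vegetables.

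**Step 3. What can be estimated.** Write the expected response to a meal as P + S, where P is the part due to the protein food and S the part due to the accompanying ingredients. The within-man contrast then estimates

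(P_AP − P_PP) + (S_AP − S_PP),

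plus any interaction of the two. Only two combinations are ever served: animal protein with the AP accompaniments, and soy with the PP accompaniments. The indicator for protein source and the indicator for accompaniments are therefore the same column in the design matrix, and only the sum is estimable. Separating the terms would need either S_AP = S_PP by construction, meaning common accompaniments, or a further meal that crosses the two factors. The plan has neither.

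**Step 4. Do other features of the plan help?**

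- Randomised order deals with period effects, not with meal composition.
- A larger sample makes the sum more precise but does not split it.
- A covariate for ingredients has no variation within a meal type.
- Palatability and viscosity are two properties of the whole meal. The article does not say how a difference in them would be used, and equality on both would not make the ingredients equal.

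**Step 5. Size.** Table 2 gives no amounts. The term S_AP − S_PP can be neither computed nor bounded from the document, and the share of the non-protein energy supplied by the common toast and oil is unknown.

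**The case against.** The strongest reply is that the protocol largely frames the comparison as meal against meal already. The Outcomes section defines the primary outcome as a comparison of the two test meals, the primary objective places protein source within a breakfast, and Table 2 discloses both recipes. On this view the overclaim amounts to two sentences in the Discussion, and those sentences concern energy expenditure and appetite; the language on pulse wave velocity is more cautious. This is fair and limits the reach of the point. It does not remove it, because the objectives also name protein source as the thing evaluated and the Discussion asserts the attribution outright.

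A second reply is that energy, macronutrients and fibre are matched and that whole-food meals cannot be made identical. That also stands: a whole-meal comparison is a legitimate design. Only the claim that it isolates protein is at fault.

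Three stronger readings are tempting, and the document does not support them:

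- A reader might infer that the trial's conclusion will be wrong. Protein source may well be the cause of a difference; the design just cannot show it.
- A reader might infer from the pickled cucumber that salt differs and will disturb blood pressure or arterial stiffness. The article gives no sodium content and documents no such pathway. It also documents no route by which the side ingredients would alter energy expenditure.
- A reader might take 8 of 10 as a measure of bias. It counts names on a list and gives parsley the same weight as potato.

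Whether soy can stand for plant protein, and chicken, egg and yogurt for animal protein, is a separate question of generalisability. Common side ingredients would not settle it.

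**Conclusion.** The point holds in a limited form. Protein source is fully aliased with the accompanying ingredients: 8 of the 10 distinct non-protein ingredients occur in one meal only, and every participant receives the same two recipes. The estimable quantity is the difference between two whole meals of equal energy and similar macronutrient and fibre content. Attribution to protein source alone, and the description as a "assessment of the pure effect of a high-protein meal of different sources", are not supported by the design, and the laboratory setting offered as the reason does not bear on the problem.

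The conclusion assumes that Table 2 lists the ingredients completely and that all participants receive these recipes. It assumes nothing about the direction or size of any effect of the side ingredients, which the document leaves unknown.

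**What to change.** **Wording (recommended).** In the objectives and the Discussion, replace the attribution to protein source by: *the difference between a soy-based and a chicken-egg-yogurt-based test meal matched for energy, macronutrients and fibre*. Remove the description as a pure effect, and do not extend the conclusion to plant versus animal protein in general. This changes no procedure, sample size or analysis. Its only price is a narrower claim.

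**Recipes (optional).** Before the first visit, use one common set of non-protein ingredients in both meals, as far as the matching of macronutrients and fibre allows. Trial status says that enrolment has not begun, and the meals are made in the university's own kitchen, so this is still possible. The costs are:

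- palatability and cultural fit may suffer, and the plan relies on both for adherence;
- a change that may affect the running of the study needs ethics committee approval first;
- some differences may remain, because keeping the meals matched can itself require adjustments.

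Even with common accompaniments, the conclusion should name the protein foods actually compared.
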